### Randomization and blinding

Participants are to be classified into one of the following three groups: (1) exercise intervention group, (2) stretching intervention (active control) group, and (3) usual lifestyle (time control) group (Fig. 2). Participants voluntarily choose to enroll in either the usual lifestyle group or one of two intervention groups (exercise or stretching). Assignment to the usual lifestyle or intervention group is determined based on participant preference and collected via a questionnaire administered after obtaining written informed consent. Only those who opt for the intervention arm are subsequently randomized into one of the two groups (i.e., exercise or stretching group). Randomization within the intervention arm is stratified by age, sex, and GFR stage and performed using a computer–generated randomization sequence following the completion of baseline assessments. The allocation ratio between the two intervention groups is 1:1. The random allocation sequence was generated by a study statistician (MG). Allocation of participants was conducted by an independent study investigator (YN) who had no direct contact with participants. Personnel involved in participant enrollment (KK) did not have access to the random allocation sequence at any stage, ensuring adequate allocation concealment. The investigators responsible for evaluating the primary outcome are independent of the study team and remain blinded to group allocation throughout the study period. However, due to the inherent characteristics of the interventions (structured exercise training versus stretching) and the need to describe the intervention procedures in the informed consent documents and study protocol, blinding participants to group allocation was not feasible. To mitigate the risk of performance bias, we standardized the frequency, duration, and monitoring procedures of both intervention programs.

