### Sample size calculation

The sample size calculation for this clinical trial is based on a previous study that explored the impact of a 1–year structured rehabilitation program on kidney function decline among patients with CKD, using a small sample from a TwiCs study design [49]. According to this previous study, the annual slope of eGFR (mL/min/1.73 m²/year) was approximately + 2 in the intervention group and − 3 in the control group, indicating a between–group difference of approximately 5 units per year. Assuming a standard deviation of 8, a two–sided significance level of 0.05, and a statistical power of 0.80, a total of 84 participants would be required based on a two–sample t–test.

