### Statistical analysis

All analyses will be conducted based on the intention–to–treat (ITT) principle. Statistical significance is set at *P* < 0.05. Data are expressed as mean ± standard deviations, median [interquartile range], or frequency counts (%), as appreciate. Baseline group characteristics will be compared using one–way analysis of variance or the Kruskal–Wallis test for continuous variables and the chi–square test or Fisher’s exact test for categorical variables. The eGFR slope for the 6–year pre–intervention, 1–year during–intervention, and 1–year post–intervention phases will be calculated. For calculating the eGFR slope, the repeated measurements of eGFR will be analyzed using a linear mixed model (LMM) including continuous time as a fixed effect and individual participant as a random effect (henceforth, Model 1). In addition, the slope will be estimated using a single linear regression of eGFR on time by each participant (called as Model 2) as a supplementary analysis.

For a primary analysis, the eGFR slope will be compared using the LMM including the group (exercise, stretching, and usual lifestyle), time, their interaction term, and the baseline eGFR as fixed effects and individual participant as a random effect. The eGFR slopes calculated by Models 1 and 2 will also be compared between groups using analysis of covariance, including the group as a factor and the eGFR slope of the 6–year pre–intervention phase as a covariate. The eGFR slope for the 6–year pre–intervention, 1–year during–intervention, and 1–year post–intervention phases will be performed using paired t–tests for within–group comparison.

Secondary outcomes will be analyzed using the generalized estimating equations (GEE) method, including group, categorical time point (baseline, 6 months, and 1 year), and their interaction term as factors. In each model, an unstructured (UN) correlation matrix will be used to account for within–individual correlations across time points. If the UN matrix leads to a convergence problem for numerical optimization, a simpler correlation structure will be used. The results of the GEE analysis will be presented as the marginal means with 95% confidence intervals. Pearson product–moment correlation analysis and repeated–measure correlation analysis [50] will be conducted to examine the associations between individual changes in each outcome.

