As a sensitivity analysis, multiple imputations will be applied to the missing outcome data to assess the robustness of the findings from the above analyses. In addition, pre–specified subgroup analyses based on baseline characteristics will be performed to further explore potential effect modification. Specifically, subgroup analyses will be conducted according to baseline kidney function (eGFR < 60 mL/min/1.73 m²), glycemic control status (hemoglobin A1c ≥ 6.5%), hypertension status (systolic blood pressure ≥ 140 mmHg and/or diastolic blood pressure ≥ 90 mmHg), and obesity/overweight (body mass index ≥ 25 kg/m²).

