## Discussion

With the rapid aging of the population, the recent predominant demographics of patients has also shifted towards middle–aged and older adults [3]. In this context, the current cases of CKD are mainly associated with the long–term affliction of lifestyle–related diseases, such as diabetes, hypertension, and arteriosclerosis/atherosclerosis. In addition to these pathophysiological trends, considering the progressive nature of CKD without apparent symptoms [5], there is a growing focus on implementing early preventive strategies to minimize the kidney function decline. Numerous epidemiological pieces of evidence demonstrating the independent association of physical activity, performance, and fitness with development in CKD suggest that addressing physical inactivity through regular exercise practices may play a crucial role in preventive strategies against CKD in middle–aged and older adults [29, 30]. However, there is a significant lack of evidence from interventional studies examining whether regularly performed exercise benefits aging kidney health. This TwiCs study will provide intra– and inter–individual comparisons between sedentary and active lifestyles, incorporating regular physical activity and exercise, offering insights into their impact on kidney health in middle–aged and older adults. We will also investigate the residual effects of exercise training intervention throughout the 1–year observation period, as such findings may help understand the potential of sustained preventive strategies for CKD.

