This study has several limitations that should be considered when interpreting our findings. First, due to the voluntary selection of participants into either the intervention or usual lifestyle groups before randomization, there may be potential selection bias; participants opting into intervention groups could systematically differ in baseline health status compared to those choosing the usual lifestyle group. However, as shown in Table 1, the baseline characteristics of exercise, stretching, and usual lifestyle groups were generally comparable, with no substantial differences observed among the three groups. The second concern is the risk of participant dropout. The previous study has shown a completion rate of 80% [49], but this may be optimistic. The extent of dropout could affect the generalizability of the results. To address this concern, we plan to conduct sensitivity analyses to examine the robustness of our findings. Third, the risk of type I error is increased due to the presence of multiple secondary endpoints because the multiplicity of test for the endpoints will not be controlled. Therefore, results from the secondary analyses will be interpreted cautiously and viewed primarily as hypothesis–generating rather than confirmatory. Fourth, in participants with early diabetes or pre–diabetes, transient glomerular hyperfiltration could temporarily elevate eGFR, thereby masking initial declines in kidney function. To mitigate this issue, subgroup analyses stratified by baseline glycemic control status using hemoglobin A1c thresholds (e.g., ≥ 6.5%) will be conducted. Finally, it is important to note that our participants have relatively preserved kidney function compared to populations studied in previous CKD trial [49]; hence, the magnitude of exercise–induced benefits observed in prior CKD–specific studies might not directly generalize to our study population.

In summary, this study is the first long–term RCT in the field of sports nephrology to employ the TwiCs study design. In the context of an ultra–aged society in which the prevalence of CKD is expected to continue to rise, our study provides crucial clinical and physiological insights into the role of regularly performed exercise as a primary prevention for CKD in middle–aged and older adults.

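### For the primary eGFR slope, standard multiple imputation cannot test robustness to informative dropout, and the secondary-outcome model leaves out the scheduled 24-month visit

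*Protocol article*

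**What the plan says.** Under Statistical analysis, the primary comparison is a linear mixed model for eGFR with group, time, their interaction and baseline eGFR as fixed effects and participant as a random effect. Supporting analyses are an ANCOVA of slopes from two models (one of them a separate regression for each participant) and paired t-tests between phases. For the rest, "Secondary outcomes will be analyzed using the generalized estimating equations (GEE) method", with an unstructured working correlation, a simpler fallback if it does not converge, and three time levels: baseline, 6 months and 1 year.

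The missing-data provision is one sentence: "multiple imputations will be applied to the missing outcome data to assess the robustness of the findings from the above analyses". The Discussion connects it to attrition. It cites an 80% completion rate in the earlier study, calls this possibly optimistic, and replies: "we plan to conduct sensitivity analyses to examine the robustness of our findings".

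Study design and Measurements both schedule four assessments, the last at 24 months. The Introduction gives long-term effects as one reason for the design, and the Discussion adds: "We will also investigate the residual effects of exercise training intervention throughout the 1–year observation period".

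**The concern.** There are two separate problems.

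First, the remedy for dropout may not reach the danger it is meant for. Dropout harms the primary comparison mainly when people leave for reasons tied to kidney function that nobody then measures. A likelihood mixed model and standard multiple imputation both predict the missing values from the observed ones. If that prediction is wrong, both are wrong in the same way. Close agreement would then be reported as robustness when the relevant question had not been asked.

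Unequal dropout is plausible from the Intervention section. The exercise programme asks for 3 × 60 = 180 to 3 × 75 = 225 minutes a week (the higher figure includes warm-up and cool-down), with at least one supervised session. Stretching asks for 3 × 10 = 30 to 3 × 20 = 60 minutes at home. Under Participants, invitees who declined gave reasons such as lack of time and distance from the fitness center.

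Second, the article fixes a list of time levels for the secondary outcomes that excludes a visit at which data will be collected. Whether effects on renal hemodynamics, mineral metabolism or fitness last after training stops would then have no stated analysis.

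**Working it through.** **1. The plan's own figure, used here only as a scale.** Sample size calculation: "Assuming a standard deviation of 8, a two–sided significance level of 0.05, and a statistical power of 0.80" and a difference of 5 ("indicating a between–group difference of approximately 5 units per year"). Under Randomization and blinding, "The allocation ratio between the two intervention groups is 1:1".

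- Normal approximation: n per arm = 2 × (1.960 + 0.842)² × 8² / 5² = 40.2, so 41 per arm and 82 in total.
- Exact t-test: 41.17, so 42 per arm and 84 in total, with power 0.808.

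The plan's statement that "a total of 84 participants would be required based on a two–sample t–test" is reproduced. Table 1 shows 43 + 45 = 88 randomised. If 80% completed, 88 × 0.80 = 70.4 would remain, and a t-test on them would have power of about 0.73. Missing data therefore matter here, though this point does not rest on the sample size.

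**2. What each analysis assumes, and what standard imputation adds.**

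| Analysis | Missingness assumption | Standard imputation adds |
|---|---|---|
| Primary mixed model | Missing at random, if correctly specified | Almost nothing: same assumption |
| Secondary GEE, unweighted | In general, dropout unrelated to outcomes | Relaxes it to missing at random |
| Per-participant slopes with ANCOVA; paired t-tests | Rely on those with usable slopes | Relaxes it to missing at random |

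**3. Illustrative simulation.** There were 400,000 participants per arm, visits at 0, 6 and 12 months, a true 12-month difference of 5, and SD 8 at each visit. Assumed, not from the documents: correlation 0.7 between visits, 20% missing at 12 months in each arm, and dropout in the exercise arm that is unrelated to the outcome, or depends on the 6-month value, or depends on the unseen 12-month value. Stretching-arm dropout is unrelated to the outcome throughout. One estimator stands for both likelihood and standard imputation, because in a large sample of this form they coincide. It compares visit means and is not the planned slope model.

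| Dropout in the exercise arm | Likelihood or standard imputation | GEE, unstructured | GEE, independence |
|---|---|---|---|
| Unrelated to outcome | 4.99 | 4.99 | 5.00 |
| Depends on observed 6-month value | 5.00 | 5.25 | 6.46 |
| Depends on unseen 12-month value | 6.03 | 6.10 | 7.08 |

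In the last row the missing-at-random estimate is off by 6.03 − 5 = 1.03, about 21% of the true difference (1.03 / 5), and comparing likelihood with standard imputation would not reveal it. In the middle row the GEE with the planned correlation is off by 0.25, against 1.46 under independence.

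**4. A simple size formula.** Bias in an arm's mean slope = (fraction missing) × (how much worse the unseen slopes are than predicted). For the exercise arm, with both inputs assumed:

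- 0.20 × 3 = 0.6 mL/min/1.73 m² per year
- 0.20 × 5 = 1.0, which is 20% of the planned difference of 5
- 0.30 × 5 = 1.5

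The bias in the between-group difference is the exercise-arm product minus the stretching-arm product, so similar dropout in both arms would cancel. At 20% missing in the exercise arm alone, explaining the whole planned difference would need a deficit of 5 / 0.20 = 25 per year. A true difference of 1 would need only 1 / 0.20 = 5.

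**5. Time points side by side.** Scheduled assessments: 0, 6, 12 and 24 months. GEE levels: 0, 6 and 12 months. eGFR phases: before, 1 year during and 1 year after the intervention. The year after the intervention is thus analysed for eGFR and appears in no stated model for the secondary outcomes.

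**The case against.** The strongest reply is that multiple imputation does not have to assume missing at random. The article does not state the mechanism, and imputation models and departure scenarios are commonly left to an analysis plan that is not shown. This stands in part: their absence alone would be no finding. What remains is that the article offers sensitivity analyses as its answer to dropout and names only imputation. If that is done in the standard way, it does not answer the question for the primary outcome. Auxiliary variables could weaken the assumption but would not test it.

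A second reply is that leaving the programme is not the same as missing eGFR. Analysis is by intention to treat and cohort measurements continue. This also stands, and it may keep the missing fraction small; it does not change what the imputation can show.

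Four stronger readings are tempting and not supported:

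- **That imputation merely repeats every analysis.** It covers all the preceding analyses, and for the GEE, the per-participant slopes and the paired t-tests it relaxes the assumption.
- **That no residual-effect analysis exists.** A 1-year post-intervention eGFR slope is planned, with paired t-tests across phases. The Discussion does not promise the same for each secondary outcome.
- **That the GEE is unsound and must be replaced.** Dropout that depends only on group and time, both in the model, does not bias it. The simulated bias with the planned correlation was small, and the Discussion calls the secondary results hypothesis-generating. A mixed model would add a normality assumption and would not address informative dropout.
- **That the plan expects at least 20% dropout.** It reports another study's completion rate and says only that this may be optimistic.

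**Conclusion.** The point holds in two limited parts. For the primary eGFR slope, standard multiple imputation shares the mixed model's missing-at-random assumption, so their agreement would not be evidence against informative dropout, the concern that the Discussion sets out to answer. This assumes imputation in its usual form and a correctly specified mixed model. For the secondary outcomes, the stated time levels conflict with the assessment schedule and leave the follow-up year without a model.

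The size of the first part cannot be known from the documents. Under the assumed inputs it is 0.6 to 1.5 mL/min/1.73 m² per year in the exercise arm, and about 1.0 on the simulated difference of 5. These are illustrations, not predictions. Even the direction assumes that faster decliners leave the exercise arm. Distortion on this scale would not create the planned difference of 5, but it could account for a much smaller one. That matters because the Discussion warns that benefits seen in patients with CKD may not carry over to this population. The change is worth making; the main analyses need not be replaced.

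**What to change.** 1. **Primary outcome.** State the assumption behind the planned imputation, and run it also under departures from missing at random. One option is delta adjustment: worsen the imputed slopes of exercise-arm participants with missing eGFR in steps, and report the tipping point at which the conclusion changes. Another is control-based imputation, in which their missing values follow the stretching arm. Either or both will serve.
2. **Secondary outcomes.** Add 24 months as a visit level in the GEE and report the group contrast there. GEE may stay as the method. Four visits instead of three raise the unstructured correlations from 3 to 6 (4 × 3 / 2 against 3 × 2 / 2), so convergence may fail more often. Naming the fallback in advance is sensible, since under independence the simulated bias was larger.

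The cost is a little more analysis. No extra visits, participants or measurements are needed.

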## Results

The demographic and clinical characteristics at the time of allocation of participants who completed the baseline assessment are presented in Table 1. At baseline, the exercise, stretching, and usual lifestyle groups were similar with respect to age, proportion of women, height and weight, body mass index, eGFR, blood biochemistry, blood pressure, and heart rate.

**Table 1 Tab1:** Baseline characteristics of exercise, stretching, and usual lifestyle groups

	Exercise (*n* = 43)	Stretching (*n* = 45)	Usual lifestyle (*n* = 53)
Age, years	68±9	67±10	69±9
Women, n (%)	32 (74)	32 (71)	37 (70)
Height, cm	157±6	160±10	158±8
Weight, kg	56.3±12.4	57.6±13.6	53.5±10.4
Body mass index, kg/m^2^	22.6±4.1	22.4±4.1	21.2±2.9
Serum cystatin C, mg/dL	0.84±0.19	0.85±0.21	0.92±0.35
eGFR_cys_, mL/min/1.73m^2^	85±19	86±19	81±23
Total cholesterol, mg/dL	220±39	220±37	227±44
HDL cholesterol, mg/dL	76±20	76±19	78±18
LDL cholesterol, mg/dL	122±30	117±27	126±36
Triglyceride, mg/dL	83±35	100±54	84±26
Fasting blood glucose, mg/dL	84±14	90±16	91±16
Hemoglobin A1c, %	5.44±0.43	5.53±0.53	5.48±0.45
Systolic blood pressure, mmHg	125±16	122±15	122±16
Diastolic blood pressure, mmHg	73±8	72±9	72±11
Pulse pressure, mmHg	52±11	50±9	50±9
Heart rate, bpm	60±7	60±9	62±9

Values are presented as the means ± standard deviation or frequency counts (percentage)

eGFR_cys_, estimated glomerular filtration rate calculated based on serum cystatin C levels; HDL, high–density lipoprotein; LDL, low–density lipoprotein

## Discussion

With the rapid aging of the population, the recent predominant demographics of patients has also shifted towards middle–aged and older adults [3]. In this context, the current cases of CKD are mainly associated with the long–term affliction of lifestyle–related diseases, such as diabetes, hypertension, and arteriosclerosis/atherosclerosis. In addition to these pathophysiological trends, considering the progressive nature of CKD without apparent symptoms [5], there is a growing focus on implementing early preventive strategies to minimize the kidney function decline. Numerous epidemiological pieces of evidence demonstrating the independent association of physical activity, performance, and fitness with development in CKD suggest that addressing physical inactivity through regular exercise practices may play a crucial role in preventive strategies against CKD in middle–aged and older adults [29, 30]. However, there is a significant lack of evidence from interventional studies examining whether regularly performed exercise benefits aging kidney health. This TwiCs study will provide intra– and inter–individual comparisons between sedentary and active lifestyles, incorporating regular physical activity and exercise, offering insights into their impact on kidney health in middle–aged and older adults. We will also investigate the residual effects of exercise training intervention throughout the 1–year observation period, as such findings may help understand the potential of sustained preventive strategies for CKD.

A key difference between the handful of previous interventional studies examining the effects of exercise training on kidney health in individuals with or without CKD and our study is the fact that our study has the long–term observational data spanning six years before intervention initiation. This difference is important for addressing the clinical question of whether exercise can improve deteriorating kidney health, which has worsened over several years owing to aging and long–term lifestyle disruptions. To our knowledge, only one pilot study has been conducted with a similar design comparing changes in kidney function before and after the intervention, suggesting that exercise training can slow the progressive deterioration in kidney function in patients with CKD [49]. However, this pilot study had a small sample size (*n* = 20) and short pre–intervention follow–up period (one year) and did not conduct follow–up measurements after the intervention. Therefore, we aimed to address these limitations by adopting a better design (i.e., TwiCs) to clarify whether exercise improves, does not affect, or deteriorates kidney health.

Emerging evidence suggests that the deterioration in renal hemodynamics [12] and mineral metabolism [13] observed in early middle age may contribute to the rapid kidney function decline in later life. Based on these findings, preventive measures to minimize the deterioration of renal hemodynamics and mineral metabolism may lead to improved long–term renal outcomes. However, the long–term effects of preventive interventions on renal hemodynamics and mineral metabolism remain unclear. In this study, as a secondary outcome, we comprehensively investigated the effects of long–term structured exercise training on renal hemodynamics and mineral metabolism in middle–aged and older adults. This will allow us to provide new insights into the underlying mechanisms through which exercise training contributes to the suppression of kidney function decline.

This study has several limitations that should be considered when interpreting our findings. First, due to the voluntary selection of participants into either the intervention or usual lifestyle groups before randomization, there may be potential selection bias; participants opting into intervention groups could systematically differ in baseline health status compared to those choosing the usual lifestyle group. However, as shown in Table 1, the baseline characteristics of exercise, stretching, and usual lifestyle groups were generally comparable, with no substantial differences observed among the three groups. The second concern is the risk of participant dropout. The previous study has shown a completion rate of 80% [49], but this may be optimistic. The extent of dropout could affect the generalizability of the results. To address this concern, we plan to conduct sensitivity analyses to examine the robustness of our findings. Third, the risk of type I error is increased due to the presence of multiple secondary endpoints because the multiplicity of test for the endpoints will not be controlled. Therefore, results from the secondary analyses will be interpreted cautiously and viewed primarily as hypothesis–generating rather than confirmatory. Fourth, in participants with early diabetes or pre–diabetes, transient glomerular hyperfiltration could temporarily elevate eGFR, thereby masking initial declines in kidney function. To mitigate this issue, subgroup analyses stratified by baseline glycemic control status using hemoglobin A1c thresholds (e.g., ≥ 6.5%) will be conducted. Finally, it is important to note that our participants have relatively preserved kidney function compared to populations studied in previous CKD trial [49]; hence, the magnitude of exercise–induced benefits observed in prior CKD–specific studies might not directly generalize to our study population.

In summary, this study is the first long–term RCT in the field of sports nephrology to employ the TwiCs study design. In the context of an ultra–aged society in which the prevalence of CKD is expected to continue to rise, our study provides crucial clinical and physiological insights into the role of regularly performed exercise as a primary prevention for CKD in middle–aged and older adults.

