**Results:**

The primary outcome is the slope of the estimated glomerular filtration rate (eGFR) based on serum cystatin C. The secondary outcomes include renal hemodynamics, mineral metabolism, cardiovascular function, body composition, muscle strength, and physical performance. At baseline, the exercise, stretching, and usual lifestyle groups were well matched for key demographic and clinical characteristics, such as age, proportion of women, and eGFR.

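### Similar measured baselines in Table 1 do not answer the selection bias from participants choosing usual lifestyle, and the planned contrasts with that group adjust for little beyond eGFR history

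*Protocol article*

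**What the plan says.** Methods, Randomization and blinding, forms the groups in two steps. First, "Assignment to the usual lifestyle or intervention group is determined based on participant preference". Then, "Only those who opt for the intervention arm are subsequently randomized into one of the two groups". The usual-lifestyle group (n = 53) is therefore self-selected, and the exercise (n = 43) and stretching (n = 45) groups are a randomised split of the 88 who chose an intervention.

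The Discussion lists this as its first limitation and replies by pointing to Table 1: "baseline characteristics of exercise, stretching, and usual lifestyle groups were generally comparable, with no substantial differences observed among the three groups". Results says the same, that the "groups were similar with respect to age, proportion of women, height and weight, body mass index, eGFR, blood biochemistry, blood pressure, and heart rate". No analytic remedy for this limitation is given beside that reply.

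Statistical analysis plans a three-group check: "Baseline group characteristics will be compared using one–way analysis of variance or the Kruskal–Wallis test for continuous variables", and "Statistical significance is set at *P* < 0.05". The primary mixed model has a three-level group factor, time, group by time, and baseline eGFR. A further analysis of covariance compares slopes with the pre-intervention slope as covariate.

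**The concern.** People who opt into a year of training or stretching may differ from those who decline in health, motivation and expected kidney trajectory. A table of measured means can show that some differences are small. It cannot show that unmeasured ones are absent.

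The usual-lifestyle group also sits in the primary model as a third level of the same factor as the two randomised arms. A reader could give its slope contrast the same standing as the randomised one, although it is an observational comparison with little adjustment for baseline health.

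**Working it through.** **Plan's own figure.** The article gives no figure for baseline balance and no size of imbalance that would count as substantial. Its only design figure, a total of 84, reproduces (difference 5, SD 8: power 0.798 at 41 per arm, 0.808 at 42) but does not bear on this point.

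**Step 1: the contrast that reflects the choice.** Inputs are the Table 1 means, SDs and group sizes. Subscripts are E for exercise, S for stretching, U for usual lifestyle.

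- Combined mean: m = (43·x_E + 45·x_S)/88
- Combined variance: s² = [42·s_E² + 44·s_S² + 43(x_E − m)² + 45(x_S − m)²]/87
- Standardised difference: |m − x_U| / √[(s² + s_U²)/2]

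For body mass index, m = (43 × 22.6 + 45 × 22.4)/88 = 22.50 and s = 4.08. The difference is (22.50 − 21.2)/√[(4.08² + 2.9²)/2] = 1.30/3.54 = 0.37.

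| Variable | Chose intervention (n = 88), mean (SD) | Usual lifestyle (n = 53), mean (SD) | Standardised difference |
|---|---|---|---|
| Body mass index | 22.50 (4.08) | 21.2 (2.9) | 0.37 |
| Weight | 56.96 (12.97) | 53.5 (10.4) | 0.29 |
| Cystatin C | 0.845 (0.199) | 0.92 (0.35) | 0.26 |
| Fasting glucose | 87.07 (15.27) | 91 (16) | 0.25 |
| eGFR | 85.51 (18.90) | 81 (23) | 0.21 |

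The SD of cystatin C, the marker behind the primary outcome, is 0.35 in the usual-lifestyle group against about 0.20 in the others.

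**Step 2: where the glucose gap comes from.**

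- Exercise vs usual lifestyle: 7/√[(14² + 16²)/2] = 7/15.03 = 0.47
- Exercise vs stretching (randomised): 6/15.03 = 0.40
- Stretching vs usual lifestyle: 1/16 = 0.06

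Most of the 0.47 arises between the two randomised arms.

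**Step 3: what the planned three-group test could show.** Let usual lifestyle differ by d SD from both other groups. The noncentrality is λ = d² × (88 × 53)/141 = 33.08·d², and the critical value of F(2, 138) is 3.06. The values of d are assumptions, shown as a range.

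| d (SD) | λ | Three-group ANOVA misses it |
|---|---|---|
| 0.5 | 8.27 | 27.7% |
| 0.4 | 5.29 | 48.1% |
| 0.37 | 4.53 | 54.6% |
| 0.3 | 2.98 | 68.7% |
| 0.2 | 1.32 | 84.1% |

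A two-group test of 88 against 53 would miss 0.5 SD 18.5% of the time. For body mass index the three-group ANOVA rebuilt from Table 1 gives p = 0.13, while the 88-versus-53 comparison gives p = 0.029 (Welch) or 0.045 (equal variance). The three-group form dilutes the contrast of interest.

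**Step 4: what the models adjust for.** In the primary model the interaction is between group and time; baseline eGFR enters as a main effect. A main effect shifts a participant's level, not the rate of change, so it does little to adjust the group-by-time contrast. The analysis of covariance adjusts the slope for pre-intervention slope. Neither names body mass index, glycaemia, blood pressure, age or sex.

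**The case against.** The case for leaving the text alone is substantial, and several parts of it stand.

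- **The bias is disclosed.** Preference-based allocation is stated plainly and selection bias is the first limitation. This stands, but the reply offered does not resolve it.
- **The differences are modest.** Of the 16 continuous variables in Table 1, only body mass index exceeds 0.30 SD on 88 versus 53; haemoglobin A1c differs by 0.01. If the 16 tests were independent and no true difference existed, at least one p-value as small as 0.029 would appear with probability 1 − 0.971^16 = 0.38. The randomised arms show gaps of the same order (glucose 0.40, triglyceride 0.37, height 0.36). Calling the groups generally comparable is defensible as description. The point rests on what comparability can prove, not on significance.
- **The Abstract is narrower.** Its statement that "usual lifestyle groups were well matched for key demographic and clinical characteristics" gives age, proportion of women and eGFR as examples. On 88 versus 53 these are 0.16 SD, 73% vs 70%, and 0.21 SD, so Table 1 does not contradict it.
- **Part of the bias is handled.** The analysis of covariance on pre-intervention slope takes up much of whatever stable health differences do to the slope. It does not cover motivation or changes that coincide with enrolment.

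Three stronger readings are tempting but unsupported. A reader might infer that self-selection produced an imbalance of 0.47 SD in glucose; Step 2 shows that this gap is mainly between randomised arms. A reader might infer that the authors rest their case on a non-significant test; the Discussion cites Table 1, which carries no p-values, so the miss rates show only that such a test would not rescue the claim. A reader might infer a doubled share of low eGFR in the usual-lifestyle group; Table 1 gives no such share, and deriving one needs a normality assumption that the cystatin C spread makes doubtful.

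**Conclusion.** The point holds in limited form. Comparability on Table 1 is not an adequate answer to self-selection, and the planned usual-lifestyle contrasts have little covariate adjustment. The visible imbalance on the choice contrast is modest, 0.21 to 0.37 SD for the five variables tabulated above, and its effect on the eGFR slope cannot be sized or signed from the article.

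The standardised differences rest on rounded Table 1 values and could move by a few hundredths. The miss rates assume normal data with equal variances and a shift of usual lifestyle from both other groups.

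A reader might conclude that the whole trial is confounded. It is not: exercise versus stretching is randomised, and the first hypothesis compares the exercise group with its own earlier slope. Neither depends on balance with usual lifestyle. The change should be made, but it concerns one set of contrasts.

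**What to change.** 1. In the Discussion, stop presenting the absence of substantial differences as the answer to selection bias. Say that measured baselines were broadly similar and that self-selection remains possible.
2. Report standardised differences for the 88 who chose an intervention against the 53 who chose usual lifestyle, including pre-intervention eGFR slope. Do not rely on the three-group test to establish balance.
3. For contrasts with usual lifestyle, add an analysis adjusted for baseline variables already collected, such as age, sex, body mass index, glycaemia, blood pressure, baseline eGFR and pre-intervention slope. Enter them with time interactions, or use weighting.
4. Label those contrasts observational, and keep exercise versus stretching as the randomised comparison.

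The cost is some wording and one further analysis on existing data, a few degrees of freedom, and a weaker statement about comparability. Adjustment will not remove unmeasured self-selection, which is why the label is needed as well.
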